**Informed consent**

The participant must personally sign and date the latest approved version of the Informed Consent form before any study specific procedures are performed.

Written versions of the Participant information sheet and Informed Consent form will be verbally discussed and presented to the participants detailing no less than: the exact nature of the study; what it will involve for the participant; the implications and constraints of the protocol; any risks involved in taking part. It will be clearly stated that the participant is free to withdraw from the study at any time for any reason without prejudice to future care, without affecting their legal rights, and with no obligation to give the reason for withdrawal.

The participant will then be given time to consider the information, and will have the opportunity to question the Investigator, their GP or other independent parties to decide whether they will participate in the study.

Written Informed Consent will then be obtained by means of participant dated signature and dated signature of the person who presented and obtained the Informed Consent. The person who obtained the consent must be suitably qualified and experienced and have been authorised to do so by the Principal Investigator. A copy of the signed Informed Consent form will be given to the participant. The original signed form will be retained at the study site.

### **Settings and locations**

The setting for the study will be split between the clinical gait laboratory at Coach Lane Campus, Northumbria University (for assessment visits) and participant's home address (for intervention sessions).

The Clinical Gait Laboratory is a dedicated facility for the investigation of gait, balance and mobility in healthy and clinical populations linking with the research themes of the Department of Sport, Exercise and Rehabilitation. The facility has all of the necessary equipment and space to allow this study to be conducted. Qualified physiotherapists will be present during the assessment visits. Reasonable travel expenses will be paid to participants for visits to the Gait Laboratory, with reimbursement based on the production of receipts, pre-paid taxi, or mileage allowances as appropriate.

### **ASSESSMENTS**

A repeated measure design will be employed with assessments performed at the clinical gait lab on two separate sessions lasting between 2-3 hours. Participants will attend the lab for outcomes to be measured at the start (baseline) and at the end of the first 4 week intervention. Results will be compared between the groups.

1. Baseline assessment (up to 180 mins)
  - Initial screening and standard clinical assessments
  - Sensorimotor assessment using Senaptec Sensory Station (SSS)
2. Follow-up assessment (after 4 week intervention) (up to 180 mins)
  - Standard clinical assessments
  - Sensorimotor assessment using Senaptec Sensory Station (SSS)

### **Initial Screening and Clinical Assessment Protocol**

#### **Past Medical History Interview**

The principal investigator or one of the investigators acting as his or her representative will provide the participants with the necessary oral and written explanations to obtain their signed/written informed consent before beginning the study.

Each participant will then be interviewed by a member of the study team. The interview will include questions regarding education level, falls history, activity level and side dominance as well as basic demographics such as age and gender.

Evaluation of cognition, visuomotor ability, disease severity, physical performance and quality of life will be performed by a physiotherapist from the research team with the following measures:

### **Neuropsychological Tests**

#### ***Geriatric depression scale (GDS-15) (Appendix 4)***

The short form GDS-15 which was created in 1986 by Sheikh and Yesavage will be used to evaluate subjects depression. This involves 15 questions about the mood of the subjects. Scores of 0 to 4 to be in the normal range, 5 to 9 to indicate mild depression, and 10 to 15 to indicate moderate to severe depression.

#### ***Montreal cognitive assessment (MoCA) (Appendix 5)***

Cognitive function will be assessed using standardized neuropsychological tests such as the MoCA; a rapid screening instrument for global cognitive dysfunction. Different cognitive domains are assessed (attention and concentration, executive functions, memory, language, visuo-constructional skills, conceptual thinking, calculations, and orientation). The MOCA was found to be a valid instrument for cognitive screening in MCI and PD. In this study the MoCA will be used as a descriptive measure.

#### ***The Penn Parkinson's Daily Activities Questionnaire-15 (PDAQ-15) (Appendix 6)***

The PADQ-15 is a 15-item measure of cognitive instrumental activities of daily living for PwP derived from the original 50-item PDAQ. It shows good discriminant validity across cognitive stages, correlates highly with global cognitive performance, and appears suitable to assess daily cognitive functioning in Parkinson's disease.

#### ***Attention Computer Battery***

A computerised battery will be used to examine attention, via simple button pressing tasks that measure reaction time, such as simple reaction time, choice reaction time and digit vigilance. The attention battery is a valid means of testing attention and has been used in a number of studies involving both PD and cognitively impaired individuals. The attention battery involves a series of computerised tests, which the subjects respond to on screen stimuli by pressing one of two buttons.

#### ***Trail Making Test (TMT) Parts A and B (Appendix 7)***

The Trail Making Test is a visual attention assessment that has been used within various neurological and cognitively impaired groups since the 1940s. The test is done in two parts; A and B. The patient is

asked to draw lines to consecutively numbered circles on one work sheet (Part A) and then to connect the same number of consecutively numbered and lettered circles on a separate work sheet, alternating between the two sequences (Part B). Subjects are told to work quickly and not to deviate from the appropriate sequence. The examiners test the subjects and record the time, in seconds, needed to complete each part of the test. Any errors are counted and corrected by the examiner, with the timer still going during correction time.

### ***Benton's Judgement of Line Orientation Test (JLO) (Appendix 8)***

The JLO is a high test-retest reliability test and has been shown to have good neuropsychological construct validity via neuroanatomical localization studies[1]. JLO is a test of visuospatial ability, which involves a subject viewing a set of numbered lines and then being shown two lines of the same orientation. They then have to name the numbers that the shown lines correspond to.

### ***Clock copying (e.g. Royall's CLOX 1 and 2) (Appendix 9)***

Clock drawing (CLOX 1 and 2) test is a measure of cognitive impairment, which is an internally consistent measure that is easy to administer and has good reliability between raters. Clock drawing is seen as a visuospatial task linked with right parietal pathology. Participants are required to draw a clock with the numbers and arrows pointed at a particular time. Then the subjects have to copy a clock drawn by the researcher.

## **Visual Sensory Functions**

### ***Visual acuity (VA) (LogMAR)***

VA is measured binocularly using a standard LogMAR chart. Participants will be seated at a distance of 4m from the chart. Participants will be instructed to read aloud down the chart starting from the top left. All correct answers are recorded on a pre-set score sheet. Test is terminated if the participant makes 2 consecutive errors.

Final LogMAR calculated with the following formula:  $\text{LogMAR} = (\text{score of the line before termination}) - (0.02 \times \text{number of errors}) + (0.02 \times \text{correct answers in the terminal line})$

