## **Secondary Objectives**

- i. To examine the impact of visual training on balance and gait (walking) outcomes in people with Parkinson's.
- ii. To explore other effects related to visual training including participants' health status, quality of life, self-efficacy, levels of activity and participation.
- iii. To compare visual assessment outcomes using the Senaptec Sensory Station with standardised visual assessment tools currently used in clinical practice – a potential validation study.

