### ***Contrast sensitivity (CS) (Mars letter CS chart, Mars Percetrix™, New York, USA)***

CS will be measured using the Mars CS sheets placed on an adjustable holder. The sheet consists of 48 Latin letters of uniform height; the contrast from the white background decreases with subsequent letters. Room illumination is adjusted so that average CS sheet luminance is between 80 and 120cd/m^2 (measured via a luminance meter). Assessment is done binocularly with the average distance from the patients eyes being 50cm. Participants read aloud down the sheet starting at the top left. Errors are recorded on the pre-set score sheet and testing is terminated after 2 consecutive errors. Final logCS calculated using the following formula:

$\text{LogCS} = (\text{value of final correct letter before stopping}) - (\text{number of errors prior to stopping} \times 0.04).$

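### The visual acuity formula has both signs reversed: errors improve the recorded LogMAR and extra letters read correctly worsen it

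*Protocol*

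**What the plan says.** Under Visual Sensory Functions, the Protocol states: "VA is measured binocularly using a standard LogMAR chart". It continues: "Participants will be instructed to read aloud down the chart starting from the top left". The stopping rule is: "Test is terminated if the participant makes 2 consecutive errors". Correct answers go on a pre-set score sheet.

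The final LogMAR is then the score of the line before termination, with the first of these two terms subtracted and the second added: "0.02 \times \text{number of errors}) + (0.02 \times \text{correct answers in the terminal line".

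The next entry, Contrast sensitivity (CS), has its own rule, introduced by "Final logCS calculated using the following formula". It takes the value of the final correct letter and subtracts 0.04 for each error made before stopping.

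Secondary objective iii is: "To compare visual assessment outcomes using the Senaptec Sensory Station with standardised visual assessment tools currently used in clinical practice".

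**The concern.** LogMAR and logCS run in opposite directions. A higher logCS is better, so subtracting errors is right there. A lower LogMAR is better, so subtracting errors rewards them. The acuity formula uses the error sign that suits contrast sensitivity, and its terminal-line term is reversed as well.

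Acuity is one of the two chart-based measures under Visual Sensory Functions, and standard clinical assessments are made at both visits. It therefore bears on the second research aim (effects on visual function). It is also a natural clinical counterpart to the Sensory Station's visual clarity parameter in objective iii. If the chart value is mis-scored, within-line gains are recorded as losses and earlier errors as gains. The comparison with the Sensory Station would then carry a scoring error that has nothing to do with the device. The Sample Size section also says the pilot is to supply parameter estimates for a main trial, and any acuity mean or standard deviation taken forward would contain the same error.

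**Working it through.** **Inputs**

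- L: LogMAR value of the line before termination (Protocol formula).
- e: errors before the terminal line.
- c: correct letters on the terminal line.
- 0.02 per letter (Protocol formula).
- Assumption: five letters and 0.10 LogMAR per line. The Protocol does not state this, but 0.02 per letter implies it. The sign finding does not depend on it.
- Direction: lower LogMAR is better, by definition of the unit. The Protocol does not say this in words.

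**Formulas**

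- Protocol: L − 0.02e + 0.02c
- Signs reversed: L + 0.02e − 0.02c
- Difference, Protocol minus corrected: 0.04 × (c − e)

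**Step 1. Worked cases, L = 0.10**

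| e | c | Protocol | Corrected | Difference |
|---|---|---|---|---|
| 0 | 3 | 0.10 − 0 + 0.06 = 0.16 | 0.10 + 0 − 0.06 = 0.04 | +0.12 |
| 1 | 3 | 0.10 − 0.02 + 0.06 = 0.14 | 0.10 + 0.02 − 0.06 = 0.06 | +0.08 |
| 2 | 0 | 0.10 − 0.04 + 0 = 0.06 | 0.10 + 0.04 − 0 = 0.14 | −0.08 |

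**Step 2. Internal consistency of the formula.** Take L = 0.10 and e = 0, and let the participant read 0, 1, 2 or 3 letters of the next smaller line.

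- Protocol: 0.10, 0.12, 0.14, 0.16. If the whole line is read, the base becomes 0.00, so the score rises with each letter and then falls by 0.16.
- Corrected: 0.10, 0.08, 0.06, 0.04, then 0.00. It falls throughout.

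**Step 3. Check against a plain letter count.** Assume a top line of 1.0. LogMAR is then 1.10 − 0.02N, where N is the total letters read. Down to the 0.20 line there are 9 lines × 5 = 45 letters, so N = 45 − e + c.

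| e | c | N | Letter count | Corrected (L = 0.20) | Protocol (L = 0.20) |
|---|---|---|---|---|---|
| 0 | 0 | 45 | 0.20 | 0.20 | 0.20 |
| 0 | 3 | 48 | 0.14 | 0.14 | 0.26 |
| 2 | 0 | 43 | 0.24 | 0.24 | 0.16 |
| 1 | 2 | 46 | 0.18 | 0.18 | 0.22 |

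The corrected form matches the count in every case. The Protocol form matches only where c = e.

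**Step 4. Does another reading of the error count rescue the formula?** The Protocol does not say whether the two stopping errors are included. If they are, then with L = 0.10, no earlier errors and c = 3, it gives 0.10 − 0.04 + 0.06 = 0.12 against a correct 0.04. The gap shrinks to 0.08 but the direction is still wrong.

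**Step 5. Effect on a change score.** A participant with L = 0.10 and e = 0 at both visits reads no terminal letters at baseline and three at follow-up. The true change is 0.10 to 0.04, an improvement of 0.06. The Protocol records 0.10 to 0.16, a worsening of 0.06.

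**The case against.** The sign error itself is hard to contest. The signs would suit a higher-is-better score, but the heading, chart and result are all labelled LogMAR and nothing in the Protocol redefines the scale. An artefact of reading the PDF would have to flip two separate signs in a formula that is otherwise intact.

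The serious objections are about reach, and most of them stand:

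- **Standing of the measure.** The Outcomes section makes visual attention (Trail Making Test and Sensory Station) the primary clinical outcome, and its list of secondary outcomes does not name acuity. The feasibility outcomes in Appendix 20 do not use it.
- **Link to the Sensory Station.** Objective iii is described as a potential validation study. The Protocol does not pair LogMAR with visual clarity; that pairing is a reasonable inference.
- **Limited distortion.** Whole-line scores still run the right way, so ranking between participants is disturbed rather than inverted. The same formula applies to both arms, so no bias between the groups has been shown.
- **Size.** The 0.12 figure pairs no earlier errors with three terminal letters, the most possible on a five-letter line that ends in two consecutive errors. It also assumes the stopping errors are not counted.
- **Recoverability.** Acuity can be re-scored from the score sheets.

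These points limit the consequences. They do not make the formula right, and none of them is a reason to leave it uncorrected.

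**Conclusion.** The formula is wrong as written and must be corrected. Both adjustment terms have the wrong sign for a quantity called LogMAR. Counting only errors before the terminal line, the displacement is 0.04 × (c − e). It is zero when c = e and reaches 0.12 (six letters, more than one line) at c = 3 and e = 0. Counting the stopping errors changes the size, but the direction in the case checked stays wrong. An individual's change can be reversed in sign.

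The direction rests only on the definition of LogMAR. Expressing the error in lines rests on five letters and 0.10 per line. No listed primary, secondary or feasibility result depends on this formula. What is affected is the acuity data under the visual function aim and any use of them as a clinical reference in objective iii.

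**What to change.** Replace the formula with:

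LogMAR = (LogMAR value of the line before termination) + 0.02 × (errors up to and including that line) − 0.02 × (correct letters on the terminal line).

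Say explicitly that letters missed on the terminal line are not added as errors. They are already reflected in c, and adding them would count them twice. Leave the logCS formula's error sign as it is.

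Correct any scoring tool built on the present formula and re-score completed acuity tests from the stored score sheets. The cost is a one-line amendment and the re-scoring time. No new data are needed.

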### ***Contrast sensitivity (CS) (Mars letter CS chart, Mars Percetrix™, New York, USA)***

CS will be measured using the Mars CS sheets placed on an adjustable holder. The sheet consists of 48 Latin letters of uniform height; the contrast from the white background decreases with subsequent letters. Room illumination is adjusted so that average CS sheet luminance is between 80 and 120cd/m^2 (measured via a luminance meter). Assessment is done binocularly with the average distance from the patients eyes being 50cm. Participants read aloud down the sheet starting at the top left. Errors are recorded on the pre-set score sheet and testing is terminated after 2 consecutive errors. Final logCS calculated using the following formula:

$\text{LogCS} = (\text{value of final correct letter before stopping}) - (\text{number of errors prior to stopping} \times 0.04).$

### ***Senaptec Sensory Station (SSS), (Appendix 1)***

Visual and sensorimotor skills will be assessed on the Sensory Station which is a training station with a 50" screen. The SSS collects and analyses data relating to 10 sensory parameters (visual clarity/ contrast sensitivity/ depth perception/ near-far quickness/ perception span/ multiple object tracking/ reaction time/ target capture/ eye-hand coordination/ go-no-go).

### **Disease Specific / Severity Tests**

#### ***Hoehn & Yahr (H & Y) (Appendix 3)***

The Hoehn and Yahr rating scale is a widely used clinical rating scale, which defines broad categories of motor function in Parkinson's disease. All participants' will be tested who are in H & Y stages I-III.

#### ***The Unified Parkinson's Disease Rating Scale UPDRS-III (Appendix 10)***

The Unified Parkinson's Disease Rating Scale (motor sub-score) part III, will be used to assess motor and non-motor features of PD and disease severity. The UPDRS is a short clinical assessment of disease severity / motor symptoms; higher scores reflect worsening disability.

#### ***The new FOG questionnaire (new FOGQ) (Appendix 11)***

Freezing of gait (FOG) will be evaluated using the new FOG questionnaire. This is a 10 item questionnaire intended to classify freezing of gait. The questionnaire has 3 parts; distinction of freezers from non-freezers, Freezing severity, frequency and duration and impact of freezing on daily life.

#### ***Falls efficacy scale – International (FES-I) (Appendix 12)***

Fear of falling will be measured using the falls efficacy scale – international version. This is a short and valid measure of fear of falling in older adults, which assesses basic and demanding activities (both physical and social. It consists of 16 scenarios (e.g. cleaning the house) and subjects must rate their fear of falling on a scale from 1 (Not at all concerned) to 4 (Very concerned).

#### ***Parkinson's Disease Questionnaire (PDQ-39) (Appendix 13)***

This 39 item questionnaire offers a patient reported measure of health status and quality of life. It assesses how often people affected by Parkinson's experience difficulties across 8 dimensions of daily living including relationships, social situations and communication. It also assesses the impact of Parkinson's on specific dimensions of functioning and wellbeing.

### **Physical/Functional Performance Tests**

#### ***Mini Best Test (Appendix 14)***

This is a clinical balance test that has shown a high sensitivity in detecting balance impairments in elderly with Parkinson's disease. It consists of 14 items, including tasks divided into four subcomponents: anticipatory postural adjustments, postural responses, sensory orientation, and

dynamic gait. Items are scored from 0 (unable or requiring help) to 2 (normal) on an ordinal scale with the maximal total score of 28 points.

### ***Gait and balance assessments***

Participants will stand still and walk in the gait laboratory while wearing several non-invasive wearable sensors that will monitor their balance and gait. Rest breaks will be allowed as needed. Participants will complete several standing and walking tasks in the laboratory, including (but not limited to) walking under single (usual walking) and dual task (speaking while walking) conditions. A researcher will stand / walk close to participants in case of any balance loss.

### ***The Fatigue Severity Scale (Appendix 15)***

This is a nine-item questionnaire that assesses the effect of fatigue on daily living. Each item is a statement on fatigue that the subject rates from 1, 'completely disagree' to 7, 'completely agree'. It is brief, easy to administer, and demonstrates reliability and internal consistency in PwP.

### **Participation/Acceptability Measures**

#### ***Pittsburgh Rehabilitation Participation Scale (PRPS) (Appendix 16)***

The PRPS measures participants' participation in relation to the level of effort and motivation they demonstrate during a therapy session. This is an easy to administer 6-point scale whereby participants' participation is scored from 1 (none) to 6 (excellent).

#### ***Systems Usability Scale (SUS) (Appendix 17)***

This scale measures the usability of technology systems and devices by levels of agreement with ten statements that are scored using a five-point Likert scale from 'strongly disagree' to 'strongly agree'.

## **INTERVENTIONS**

Following screening and clinical assessment at the Gait Lab, participants will receive a telephone call from the researcher prior to starting the visits. This will allow participants to ask any further questions about the sessions following their assessments and to help them feel more familiar with the visiting therapist. It will also be an opportunity for the researcher to help the participant identify a suitable location in their home in which to undertake the subsequent training sessions in preparation for the first visit.

After the familiarisation phone call, the home visits will commence. Participants will be allocated to either Group A (technological visual training) or Group B (standard training). Both groups will receive two training sessions per week for four weeks in their home environment delivered by one of the researchers. Following this intervention, participants will be invited back to the Gait Lab for follow-up assessment. See *Figure 1* below for a summary for the study design.

[figure not shown]

Figure 1. Study design

### **Group A: Technological Visual Training (TVT)**

The experimental group will receive a total of 8 sessions of TVT over a 4 week period. Each session will last up to 60 min of which 20 mins will be dedicated to a series of visual training drills using a mobile tablet device (see *Appendix 18* for list of training drills), and a further 10 mins will be spent doing simple hand-eye co-ordination activities (e.g. throwing and catching) whilst wearing stroboscopic glasses. The remaining time will be factored in for rest periods as required. Activities will be supervised at all times by the researcher who will keep a running log of issues that may arise during the intervention period such as adverse events, changes in medication or any environmental factors that could affect participant engagement or performance.

